### 2.5. Sample Size

The sample size was estimated via a priori analysis using G*Power. We selected goodness-of-fit (F test) and analysis of covariance (ANCOVA) (for fixed effects, main effects, and interactions) for finding the sample fitness and size. The other data were set as α = 0.05, 1 − β (power) = 0.8, numerator df = 1, number of groups = 4, and number of covariates = 4. Based on this calculation, the minimum sample size was estimated to be 128 (64 in each group). Since the subjects were hemiplegic patients, the minimum sample size was defined as 128 subjects (64 subjects in each group).

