### 2.7. Sequence Generation

Simple randomization will be used for allocation. Once patients who meet the eligibility criteria are enrolled, they will be assigned using a random number table generated at each hospital.

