### 2.14. Statistical Analysis

A multivariate ANCOVA will be conducted to test the hypothesis that the occupational therapy intervention in this study will improve motor function in chronic stroke patients undergoing NEURO^®^ when compared with conventional occupational therapy interventions. The dependent variable will be the date or period of assessment, and the independent variables will be the change in scores of the primary assessment (FMA-UE) and the secondary assessments (ARAT and JASMID). The covariates are age, sex, BMI, and time since onset. JAMOVI version 2.2.1 (JAMOVI Project, Sydney, Australia) will be used for statistical analysis.

The primary analysis will be conducted when the intervention and control group samples reach a total of 64 cases each in all settings. The secondary analysis will be conducted when the number of patients in each group exceeds 60% of all participating centers (Figure 6).

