**Figure 6 jcm-11-06835-f006:**
[figure not shown]
Research procedure. The study setting includes 14 NEURO^®^-accredited facilities in Japan that have agreed to participate in the study. Once patients who meet the study eligibility criteria are enrolled, they will be assigned to the intervention and control groups using a random number table generated for each facility.

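### The secondary-analysis trigger compares patients with centres, so its timing is not fixed and it may fall before the primary analysis

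*Protocol article*

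**What the plan says.** Section 2.14 gives two timing rules. For the primary analysis: "The primary analysis will be conducted when the intervention and control group samples reach a total of 64 cases each in all settings". For the secondary analysis: "The secondary analysis will be conducted when the number of patients in each group exceeds 60% of all participating centers", with a reference to Figure 6. The figure's image is missing from the text reviewed. Its caption covers the setting ("The study setting includes 14 NEURO" accredited facilities) and the allocation method, and does not mention the 60%.

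Section 2.14 describes one model, a multivariate ANCOVA that takes the change in FMA-UE (primary) together with ARAT and JASMID (secondary). It does not say which outcomes or patients the secondary analysis covers, or what it is for.

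Section 2.5 sets the size: "the minimum sample size was estimated to be 128 (64 in each group"). Section 2.9 says that physicians, occupational therapists and the evaluator know the allocation, and that the analyst works on a dataset with group identity masked.

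**The concern.** The sentence sets a number of patients against a percentage of centres, and these are different units. A site team or analyst could not tell from it when the analysis is due. Because the secondary analysis has its own trigger, separate from the primary one, the text does not imply that the two are run together.

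If the trigger is met first, secondary conclusions would rest on part of the data. The article states no limit on who sees the results. Between-arm results could therefore reach open-label therapists and evaluators who are still treating patients and scoring FMA-UE and ARAT. If the one stated model were used, those results would include the primary outcome. An undefined trigger also leaves the date of the analysis open to choice after data have been seen.

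**Working it through.** **Inputs from the article.** 14 centres (2.3, 2.12, caption of Figure 6); 64 per group, 128 in total (2.5, 2.14); power 0.8 and, in 2.5, "The other data were set as α = 0.05"; "numerator df = 1, number of groups = 4, and number of covariates = 4".

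**Assumption.** Section 2.5 gives no effect size. I take Cohen's f = 0.25, which for two equal groups is a standardised difference d = 2f = 0.5.

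**1. Reproduce the plan's figure.** ANCOVA power from the noncentral F distribution, with df1 = 1, df2 = N − 4 groups − 4 covariates and λ = f²N. At N = 128: df2 = 120, λ = 0.0625 × 128 = 8.0, power 0.801. This is the smallest N that reaches 0.8. By contrast f = 0.24 needs 139 and f = 0.26 needs 119, so f = 0.25 is very probably the value used.

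**2. Put the trigger into numbers.**

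| Reading of the 60% | Calculation | Fires at | Relative to 64 per group |
|---|---|---|---|
| 60% of the target per group | 0.6 × 64 = 38.4 | 39 per group (at least 78 of 128, 61%) | before |
| Literal, against the number of centres | 0.6 × 14 = 8.4 | 9 per group (at least 18 of 128, 14%) | before; unlikely intent |
| 60% of centres contributing to both groups | 0.6 × 14 = 8.4, so 9 of 14 centres | no fixed patient number | before, at or after |

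The totals are minimum values. Section 2.7 says "Simple randomization will be used for allocation", so the two groups need not fill at the same pace.

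**3. Power if the analysis is run at 39 per group.** Same formula with N = 78, df2 = 70 and λ = (d/2)² × 78, set against N = 128, df2 = 120.

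| d | λ at 78 | Power at 39 per group | λ at 128 | Power at 64 per group |
|---|---|---|---|---|
| 0.4 | 3.12 | 0.41 | 5.12 | 0.61 |
| 0.5 | 4.875 | 0.59 | 8.00 | 0.80 |
| 0.6 | 7.02 | 0.74 | 11.52 | 0.92 |

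**4. Type I error, under a condition.** Suppose the same hypothesis is tested at two-sided 0.05 at 39 and again at 64 per group, and either result may be claimed. Under the null the two statistics are bivariate normal with correlation √(39/64) = 0.781. The probability that at least one exceeds 1.96 in absolute value is about 0.079. If the early analysis does not test that hypothesis, this figure does not apply.

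**The case against.** - **The missing figure may explain the rule.** This is possible, since the sentence points to Figure 6. Its caption does not explain the 60%, however, and the sentence would still compare unlike quantities.
- **The rule may be a centre-coverage condition.** The preceding sentence speaks of all settings, so the authors may have meant that 60% of centres have contributed patients. This stands as a fair reading. It means that one cannot say the secondary analysis always comes before the primary one, especially as 128 is called a minimum. It does not rescue the rule, because the timing then has no patient number at all.
- **A reader might infer an uncontrolled interim test of the primary outcome with inflated error.** The article does not support that. It does not call this an interim analysis, does not say that FMA-UE is tested in it, and does not let it stop or change the trial. Exposure of FMA-UE is an inference from there being only one stated model.
- **The analyst is masked.** This is true and relevant. Masking governs how the data are analysed. It does not restrict who receives the results, so it reduces the concern without removing it.
- **The effect size is not in the document.** This also stands. The value of 0.5 is inferred from the sample size, and nothing ties it to ARAT or JASMID, so the 0.80 at 64 per group is not a planned power for those outcomes.

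**Conclusion.** The point holds as a defect in a stated rule. The trigger cannot be applied as written, and its timing relative to the primary analysis is undetermined. Under the more natural numeric reading it falls at 39 per group, 25 per group short of the primary analysis. Power there is about 0.59 against 0.80 if d = 0.5 (0.41 against 0.61 at d = 0.4; 0.74 against 0.92 at d = 0.6). The 9-per-group reading is literal but improbable, and nothing should be built on it.

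Early analysis and exposure of the primary outcome by arm are possible consequences, not certain ones. The type I error of about 0.079 depends on repeat testing that the article does not describe. The sentence should be changed before the trial relies on it. Leaving details to a separate analysis plan would not cure it, because the rule is already stated here in units that do not match.

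**What to change.** Replace the 60% sentence in section 2.14 with: *All secondary analyses are done once, on the same locked dataset as the primary analysis, after the last patient's discharge evaluation.*

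If a progress check at 60% is wanted, state it in clear units, either patients per group or number of centres with patients in both groups. Limit it to pooled recruitment and data-completeness figures, with no comparison by arm.

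The change is one sentence. Its cost is that secondary results come later: under the 39-per-group reading, by the time needed to recruit the remaining 25 per group (64 − 39) and complete their two-week stay.

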### 2.15. Ethical Considerations and Declarations

All patients will provide written consent to participate in this study. This study was approved by the Jikei University School of Medicine Ethics Committee (approval number 32-33810423). The study has been registered in the Clinical Trials Registry of the University hospital Medical Information Network (UMIN) Center (UMIN Test ID: UMIN000047489).

Doctors and occupational therapists will wear masks, wash their hands and sterilize with alcohol when providing treatment.

### 2.16. Status and Timeline of the Study

This study was approved by the ethics committee and registered as a clinical trial. This study will begin in December 2022 and end in August 2024.

## 3. Discussion

We predict that the occupational therapy interventions in this study will improve patients’ motor function compared to conventional occupational therapy interventions. The occupational therapy intervention in this study specifies (1) the level of practice difficulty, (2) the amount of practice, and (3) the method of goal setting. (1) The difficulty levels of the exercise menus in the four plans are set according to the item-specific difficulty levels of FMA-UE. Functional exercises are selected in accordance with the severity of the patient’s motor paralysis [27,28,29]. (2) The amount of practice is specified with reference to studies that have verified the threshold of the number of joint movements required for the recovery of motor paralysis [19]. Patients will be provided with an adequate amount of practice according to the selected practice plan. (3) Goal setting is based on the FMA-UE scores at the initial evaluation to predict recovery; the treatment goals and the selected practice plan will be explained to the patients [23]. One of the five functional exercises will be introduced based on the patient’s preference. The patient’s understanding of the set goals and the performance of active practice are reportedly important for the recovery of motor paralysis [21,22]. Therefore, the occupational therapy intervention in this study can promote the use-dependent plasticity of patients’ brains more effectively than conventional occupational therapy interventions and is expected to improve patients’ motor functions.

If the occupational therapy intervention used in this study improves the patients’ upper limb motor function when compared to that of the conventional occupational therapy intervention, the level of practice difficulty and the amount of practice used in this study can act as a guideline to formulate a new practice method to improve the upper limb function of patients. Occupational therapists can provide a sufficient amount of joint movement exercises according to the severity of the patient’s upper limb motor paralysis to encourage use-dependent plasticity in the patient. Standardization of occupational therapy treatment content and equalization of treatment allow efficient and effective rehabilitation of patients. Improvement in motor function contributes to the improvement of the patient’s ADL (Figure 7). The results obtained after the implementation of this protocol will assure that the ADL and certain results of occupational therapy can be attained by patients with upper motor paralysis, in any facility.

This study has a few limitations. Since this study will be conducted at a facility in Japan, it is unclear whether similar results will be obtained in other countries. We speculate that there is a limitation to the generalization of this study’s results. In countries other than Japan, the medical systems are different, and it is difficult to implement the same treatment methods since insurance for hospitalization of patients with chronic stroke and the roles of doctors and therapists vary. There are also cultural differences in the ADL required by patients. Multinational studies are needed to clarify this point. In addition, the patient’s nutritional status may affect the recovery of motor paralysis. In this study, it will not be possible to obtain data on the nutritional status of patients prior to inpatient treatment.

## Figures and Tables

**Figure 1 jcm-11-06835-f001:**
[figure not shown]
Schedule of enrollment, interventions, and assessments. FMA-UE, Fugl-Meyer assessment of the upper extremity; ARAT, Action Research Arm Test; JASMID, Jikei Assessment Scale for Motor Impairment in Daily Living. Investigators will obtain informed consent from patients who meet the eligibility criteria. Patient allocation will be performed by random assignment using a table of random numbers created at each hospital. Participant characteristics and medical information will be investigated. The control and intervention groups will receive treatment for two weeks. Patients will be evaluated on the day of admission and on the day of discharge.

**Figure 2 jcm-11-06835-f002:**
[figure not shown]
Chart of procedures for determining a functional practice plan. FMA-UE, Fugl-Meyer assessment of the upper extremity. The FMA-UE Part A (shoulder flexion to 90° during elbow extension) and Part C (finger mass extension) scores, evaluated on the day of admission, are used to determine the plan of functional exercises. The functional exercise plans are classified from 1 to 4 according to the scores from the two tests.

**Figure 3 jcm-11-06835-f003:**
[figure not shown]
Item difficulty of Fugl-Meyer assessment for upper extremity. The results of three studies examining the difficulty of FMA-UE sub-items are presented. The sub-items with higher difficulty are located toward the top. A, B, C, and D next to the lower-level items indicate the corresponding subsection. As for the participants’ characteristics, Woodbury ML et al. reported that the participants were mainly patients with acute mild hemiplegia. Hijikata et al. reported that the participants were mainly patients with moderate-to-severe chronic-stage hemiplegia. Tauchi et al. reported that the participants were mainly patients with mild-to-moderate subacute-stage hemiplegia. This figure has been partly modified from the articles published by Woodbury, M.L., et al., 2007 [27], Hijikata, et al., 2020 [28], and Tauchi, et al., 2021 [29].

**Figure 4 jcm-11-06835-f004:**
[figure not shown]
Chart practice posture determination methods. A method for determining the posture of functional exercises is presented. The supine and side-lying postures are chosen when the influence of postural muscle tone reduction, trunk function, and balance function are excluded. The sitting posture is selected when the patient wants to perform upper limb and finger exercises at a desk or in an end-sitting position or when the patient wants to exclude the effects of balance function in the standing posture. The standing posture is selected when the patient’s goal is to perform ADL in the standing posture.

**Figure 5 jcm-11-06835-f005:**
[figure not shown]
Chart of methods to determine the amount of practice assistance. A method for determining the amount of assistance for performing functional exercises is presented. Passive exercise is selected when the goal is to decrease muscle tension and improve the range of motion of joints. Active assistive exercise is selected when the patient wants to suppress joint movements, limit the degree of freedom of movement, and supplement muscle output. Active resistive exercise is selected to add load to joint motion. Active free exercise is selected to perform upper-extremity movements without adding load to the joint motion.

**Figure 6 jcm-11-06835-f006:**
[figure not shown]
Research procedure. The study setting includes 14 NEURO^®^-accredited facilities in Japan that have agreed to participate in the study. Once patients who meet the study eligibility criteria are enrolled, they will be assigned to the intervention and control groups using a random number table generated for each facility.

**Figure 7 jcm-11-06835-f007:**
[figure not shown]
Expected results. ADL, activities of daily living. In the administered occupational therapy, the intervention group is defined by (1) setting the difficulty level of functional exercises, (2) providing an adequate amount of exercise, and (3) the method of goal setting. Therefore, the use-dependent plasticity can be promoted more effectively in the interventional group than in the conventional occupational therapy group, and the patients’ motor functions are expected to improve. Improvement of motor function is expected to contribute to the improvement of patients’ ADL.

**Table 1 jcm-11-06835-t001:** Demographic data of patients.

		Intervention Group	Control Group	Total
Number of patients		N = XX	N = XX	N = XX
Age		XX	XX	XX
Sex		Female = XX Male = XX	Female = XX Male = XX	Female = XX Male = XX
Height		XX	XX	XX
Weight		XX	XX	XX
BMI		XX	XX	XX
Affected side		Left = XX, Right = XX	Left = XX, Right = XX	Left = XX, Right = XX
Dominant hand		Left = XX, Right = XX	Left = XX, Right = XX	Left = XX, Right = XX
Diagnosis	CI	N = XX	N = XX	N = XX
	ICH	N = XX	N = XX	N = XX
Time from onset		XX	XX	XX
FMA-UE severity				
No (<23)		N = XX	N = XX	N = XX
Poor (≤23–≤31)		N = XX	N = XX	N = XX
Limited (≤32–≤47)		N = XX	N = XX	N = XX
Notable (≤48–≤52)		N = XX	N = XX	N = XX
Full (≤53–≤66)		N = XX	N = XX	N = XX

BMI, body mass index; CI, cerebral infarction; ICH, intracranial hemorrhage; FMA-UE, Fugl-Meyer assessment of the upper extremity.

**Table 2 jcm-11-06835-t002:** NEURO^®^ study protocol and momentum settings.

First Week	Monday	Tuesday	Wednesday	Thursday	Friday	Saturday	Sunday
**Event**	Admission						
**rTMS (pulse)**	2400	2400	2400	2400	2400	2400	-
**One-to-one training (time)**	-	500	500	500	500	500	-
**Second week**	Monday	Tuesday	Wednesday	Thursday	Friday	Saturday	Sunday
**Event**						Discharge	
**rTMS (pulse)**	2400	2400	2400	2400	2400	2400	
**One-to-one training (time)**	500	500	500	500	500	-	

rTMS, repetitive transcranial magnetic stimulation. The protocol for admission on Monday is shown. In the columns of one-to-one training, the momentum of joint exercises for the functional exercises set up in this study is shown. Patients will perform the functional exercises of one-to-one training for a total of 1000 times. Patients are exposed to a total of 28,800 rTMS stimuli and 2400 pulses per day, except on Sundays. Patients will be evaluated on the day of admission and on the day of discharge.

**Table 3 jcm-11-06835-t003:** Training menu for each plan.

	One-to-One Training	Self-Training
**Plan 1**	Scapular retraction/protraction Shoulder flexion to 0–180°, elbow extended Shoulder flexion to 0–90°, elbow extended Elbow extension _______________________	Scapular retraction/protraction Shoulder flexion to 0–180°, elbow extended Shoulder flexion to 0–90°, elbow extended Elbow extension ___________________
**Plan 2**	Shoulder flexion to 0–180°, elbow extended Shoulder flexion to 0–90°, elbow extended Elbow extension Finger extension, elbow extended _____________________	Scapular retraction/protraction Shoulder flexion to 0–180°, elbow extendedElbow extension Finger extension ______________________
**Plan 3**	Shoulder flexion to 90–180°, elbow extended Shoulder abduction to 0–180°, elbow extended Wrist flexion/extension, elbow extended Finger extension ____________________	Shoulder flexion to 90–180°, elbow extended Forearm supination/pronation Wrist flexion/extension Finger extension ______________________
**Plan 4**	Shoulder abduction to 0–180°, elbow extended Forearm supination/pronation, elbow extended Wrist flexion/extension, elbow extended Finger extension, elbow extended ______________________	Shoulder flexion to 90–180°, elbow extended Forearm supination/pronation Wrist flexion/extension Finger extension ___________________

Ten exercises are set for each of the four plans, five for one-to-one training and five for self-training. The five exercises in the blank columns are determined by the patient and the therapist based on the patient’s consent, the discussion between the patient and the therapist regarding the exercises that are expected to be highly necessary for the patient to acquire the activities of daily living, and the exercises that meet the patient’s needs. Different practice menus may be introduced for one-to-one training and self-training, but the determined practice plan and the practice menus introduced in the plan should not be changed during the hospitalization period or in the middle of the session. The posture and the amount of load during the exercises are determined according to Figure 4 and Figure 5, respectively, and the occupational therapist may change them according to the patient’s condition and the purpose of the exercises.
